### 2.6. Sample Size

The initial idea is to perform the first test on a pilot sample of 25–30 patients from each unit, with which the investigators have collaboration agreements. This pilot study is intended to evaluate the quantitative data to assess whether or not there is an improvement. At the end of the intervention, a questionnaire will be conducted through LimeSurvey (an anonymous survey platform) with open-ended questions, such as: ‘What did you like most? How do you feel after the intervention? What improvements would you suggest? What would you like to change?’ The aim is to find out patient satisfaction and to suggest improvements for the final programme. Several members of the research team will carry out the analysis of the systematic qualitative data in order to achieve a consensus.

Subsequently, modifications will be made to the programme based on the results obtained, and the programme will be applied to those adolescents and their families who regularly attend hospital outpatient clinics and meet the inclusion criteria. Once implemented in a pilot sample, this protocol will be extended to a larger sample, with a sample size of approximately 200 chronically ill adolescents and their families.

### 2.7. Recruitment

Endocrinologists, pulmonologists, and allergists will be responsible for recruitment, which will take place in the hospital during routine patient visits. Participants will be asked to complete a battery of questionnaires on their psychological and physical health statuses in a single session. The design of this intervention consists of patients and caregivers who receive the treatment program, who will act as their own control group; then, after six months, the 10Vida intervention will be initiated. The outcome measures will be collected by the medical and psychological specialists.

### 2.8. Methods: Data Collection, Management, and Analysis

Assessments at baseline, pre-intervention, and post-intervention will be performed by the medical specialists and trained psychologists working together. The following sociodemographic and clinical variables of the children and adolescents will be collected by means of an ad-hoc registry: their date of birth, age, sex, and school year. Moreover, for the main family caregivers, the following variables will be collected by an ad-hoc registry: relationship to the patient, age, and presence of chronic disease in the caregiver.

Clinical variables will also be recorded (among them, and when applicable): the main diagnosis, secondary diagnosis, time of diagnosis, time of treatment, number of hospital and/or emergency room admissions, and the total number of these admissions that are directly related to the chronic disease, as well as the type and amount of medication taken, and frequency of regular medical control visits.

#### Statistical Methods

Independent-samples *t*-tests and chi-square tests were performed to determine pre-intervention differences between participants with and without missing values in the variables studied. In addition, chi-square tests were undertaken to compare the number of people who dropped out of the research in the experimental group with those who dropped out in the control group, and it was found that they did not differ significantly.

Before testing the change models, descriptive analyses, Pearson correlations, and multivariate and univariate variance analyses (MANOVA and ANOVA) were performed with the pre-intervention scores of the participants in the experimental and control groups to identify possible differences in the baseline. Likewise, multivariate and univariate covariance analyses (MANCOVA and ANCOVA) were performed to identify changes in the post-intervention scores (short-term effect), while controlling for the pre-intervention scores (covariate). In addition, the effect size (Cohen’s *d*) of each variable was calculated to estimate the magnitude of the differences between the experimental and control groups. These analyses were performed with the statistical package SPSS V.26.

Multiple hierarchical regression analyses were conducted to examine the added predictive value of the experimental condition to explain the effectiveness of the intervention programme [46]. Firstly, the pre-intervention assessment score (control variable) was introduced, and then the experimental condition (1 = experimental intervention group, 0 = control group) was introduced as an independent variable. The dependent variable was the change variable between pre- and post-interventions, as well as between pre-intervention and the follow-up of the emotional and well-being variables. In this sense, the statistically significant change of the determination coefficient in model 2 (predictor: experimental condition, controlling for the pre-intervention score) is interpreted as an added predictive value. The significant prediction of the experimental condition, controlling for the pre-intervention score, leads us to attribute the significant change to the intervention. All data shall be entered electronically. Participant files will be recorded securely and will be stored for a period of 10 years after the end of the study.

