### 2.3. Interventions

10Vida is a program that consists of different psychological objectives to be applied to adolescents between 12 and 16 years of age who suffer from a chronic disease thatincludes the pneumo allergic or endocrinological specialties. It is a 7-session intervention programme (five individual sessions with adolescents, and two sessions with family caregivers) consisting of one session per month with patients, and two sessions at the end of the treatment with family caregivers (month 4 and month 5).

It is a program that provides strategies and tools, trying to provide answers to the needs of the adolescent and caregivers, which can facilitate adherence to treatment and, therefore, improve physical and psychological health. It has been shown that a psychological intervention is necessary in addition to the important medical treatment, as it improves the emotional well-being of the adolescent and their families. 10Vida consists of individual sessions for both adolescents and their families, such as parents as caregivers who may be overloaded with tasks, worries, and the need to help their child to be happy. The specific objectives of each of the adolescent and caregiver sessions, as well as the areas to be worked on, are shown in Table 2. In addition, a summary of the strengths promoted by the programme are shown in Figure 1. To work on the different session objectives, various activities or tasks have been developed with different objectives to improve each of the key areas of the sessions. All activities can be found in Table 3. Participants who do not complete 80% of the sessions will be excluded from the study.

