### 2.5. Participants’ Timeline

The first pilot study started in February 2019, following the proposed structure with a small sample of six participants (adolescents and their families), and it was concluded in January 2020. Due to the pandemic, this protocol had to be adapted to a fully online format while maintaining the activities and variables studied. Currently, the February 2022 participants are being recruited for a second pilot study to test the intervention and improve the programme. The main study is scheduled to run from September 2022 to September 2024. Table 1 shows the timeline for the enrolment, interventions, and evaluations. The main objectives of phase I are the selection of the hospitals, the request for informed consent, and the baseline assessment. Firstly, the services of the hospitals that the research team has convened will be contacted. After meetings with the directors, informed consent will be requested from the families and adolescents participating in the programme. Before implementation, patients will be asked to complete a set of questionnaires. Phase II’s main objective is to evaluate the participating patients and family members, as they will constitute the control group. After six months, in phase III, the main objective will be implementing the intervention programme in the same sample as in phase II. After completing the intervention, in phase IV, participants will be re-evaluated. In the last phase, the effectiveness of the programme will be analysed.

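### The protocol reports as a finding that dropout was balanced between two groups, but it names no dataset or counts, and the one-group design contains no such groups

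*Protocol article*

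**What the plan says.** Section 2.8, Statistical Methods, describes chi-square tests of the number of people lost from an experimental group against "those who dropped out in the control group, and it was found that they did not differ significantly". No sample, numerator, denominator, test statistic or p-value accompanies the statement.

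Section 2.5 gives the state of the programme when the article was written:

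- The first pilot ran from February 2019, "with a small sample of six participants (adolescents and their families), and it was concluded in January 2020".
- A second pilot was under way: "Currently, the February 2022 participants are being recruited for a second pilot study to test the intervention and improve the programme".
- Still ahead at that point was the full trial: "The main study is scheduled to run from September 2022 to September 2024".

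Section 2.6 places the large sample after the pilot: "this protocol will be extended to a larger sample, with a sample size of approximately 200 chronically ill adolescents and their families".

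On the control condition, section 2.7 describes patients and caregivers "who receive the treatment program, who will act as their own control group". Section 2.1 says the same, and Table 1 marks allocation as not applicable. Section 2.3 adds a removal rule: "Participants who do not complete 80% of the sessions will be excluded from the study".

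**The concern.** Two things are wrong with the sentence.

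First, it is a result, not a method. Most of Statistical Methods is in the past tense and could be read as a slip for the future. This clause cannot, because putting its verbs in the future would predict the outcome of a test. Nothing in the article lets a reader check it.

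Second, the test presupposes two separate groups. The trial has one group observed over two successive six-month periods: a wait (T1 to T2) and a treatment period (T2 to T3), in the labels of section 2.1.

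Attrition matters here because the change from T2 to T3 carries the treatment effect, and Statistical Methods attributes a significant change to the intervention. If those who leave during treatment differ from those who stay, the change among completers can arise from selection. Loss during treatment is also evidence on acceptability. A statement that attrition is balanced should therefore rest on visible numbers.

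**Working it through.** **Step 1: can the stated result be reproduced?** No. The article gives no counts, group sizes or p-value. Section 3 mentions preliminary findings from a pilot in type 1 diabetes, and the Data Availability statement offers preliminary data on request. Neither gives a dropout figure.

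**Step 2: what could a test in six people show?** Assumptions, none of which the article states: the six participants of the first pilot are the source; each counts once in each period; the periods are treated as independent groups of 6; alpha is two-sided 0.05. For no loss in the wait (0/6) against k/6 in treatment:

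- Fisher, two-sided: 2 × C(6,k)/C(12,k). At k = 4 this is 2 × 15/495 = 0.061.
- Pearson: N(ad − bc)²/(product of the four margins). At k = 4, 12 × 24²/(6 × 6 × 4 × 8) = 6.0, p = 0.014.
- With continuity correction: 12 × (24 − 6)²/1152 = 3.375, p = 0.066.

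| Lost in treatment | Fisher | Corrected chi-square | Uncorrected chi-square | Smallest expected count |
|---|---|---|---|---|
| 3 of 6 | 0.18 | 0.18 | 0.046 | 1.5 |
| 4 of 6 | 0.061 | 0.066 | 0.014 | 2.0 |
| 5 of 6 | 0.015 | 0.019 | 0.003 | 2.5 |

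Uncorrected chi-square crosses 0.05 at 3 of 6, but its expected counts are too small for the approximation to be trusted. Fisher and the corrected test cross at 5 of 6.

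**Step 3: other ways of counting the six.**

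- Split 3:3, the most extreme table (3/3 against 0/3) gives Fisher 2 × 1/C(6,3) = 2/20 = 0.10 and corrected chi-square 0.10.
- Split 2:4, the most extreme table (2/2 against 0/4) gives Fisher 1/C(6,2) = 1/15 = 0.067 and corrected chi-square 0.126.
- Uncorrected chi-square gives 0.014 for both tables, on expected counts no larger than 1.5 for dropouts in the smaller cells.
- A sign test within people, five losses in treatment against none in the wait, gives 2 × (1/2)⁵ = 0.0625.

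**Step 4: power at 6 against 6, for assumed dropout rates.**

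| Assumed loss | Fisher power | Uncorrected chi-square power | n per group for 80% power |
|---|---|---|---|
| 30% vs 10% | 0.6% | 14% | 62 |
| 40% vs 10% | 2.3% | 26% | 32 |
| 50% vs 10% | 6.4% | 39% | 20 |

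The last column uses n = [1.96√(2p̄(1 − p̄)) + 0.8416√(p₁(1 − p₁) + p₂(1 − p₂))]²/(p₁ − p₂)². For 30% vs 10%: (1.109 + 0.461)²/0.04 = 61.6, rounded up to 62.

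**Step 5: does the comparison fit the design?** Under sections 2.1 and 2.7 and Table 1 the same people pass through the wait and then treatment. Someone lost in the wait is not at risk of loss in treatment, so the denominators are nested: if one of six left during the wait, 6 − 1 = 5 would be at risk afterwards. An independent-groups chi-square ignores this. In addition, sessions are held only after T2, so the 80% rule can remove people only in the treatment period. The two periods do not have the same routes to loss.

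**The case against.** A reader might infer that the result was written before any data existed. The documents do not support that. The first pilot ran for about a year, long enough for a wait and a treatment period, and the article refers to preliminary findings and preliminary data. The sentence does not say that it concerns the main study. What stands is narrower: the source is not identified and no counts are given, while the second pilot and main study could not yet have supplied them.

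A reader might also take 5 of 6 as the loss needed for significance. That holds only for Fisher or the corrected test with the same six people treated as two independent sixes. The article names chi-square without a correction, and it is unclear whether its six participants include caregivers. No single threshold can be defended; the conclusion that about six people show little survives.

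It would go too far to say that the clause licenses the trial to ignore withdrawal. No analysis step depends on it. The preceding sentence compares participants with and without missing values, and section 3 concedes that results may not be attributable to the programme and that numbers may be small.

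Finally, whether removals under the 80% rule count as dropouts could be left to an analysis plan that is not shown. That is fair, so the rule is a secondary point here. No analysis plan, however, would make the unsupported result in the article right, or give the design a separate control group.

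**Conclusion.** The point holds. The article asserts a non-significant dropout comparison that cannot be traced to any data shown, and frames it between two groups that its own design does not have. If the six-participant pilot is the source, which is an inference, the result carries almost no information. Fisher power is below 7% even for 50% against 10% loss, and below 40% with the uncorrected test, whose approximation is unreliable at these counts. These figures rest on assumed dropout rates, a two-sided 0.05 level and the 6-against-6 layout, and are illustrative. The mismatch between the test and the one-group design depends on none of them. The fault lies in one sentence and the test it describes, and it bears on what the trial may conclude about attrition.

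**What to change.** 1. Delete the result clause that ends the dropout sentence in Statistical Methods. Alternatively, name the pilot dataset and give its counts.
2. Replace the between-group chi-square with a description by period: number and percentage lost from T1 to T2, of those assessed at T1, and from T2 to T3, of those assessed at T2, each with a 95% interval and reasons. Use the section 2.1 labels; section 2.4 calls the same visits T0, T1 and T2.
3. Show removals under the 80% session rule as a separate line within T2 to T3 loss.
4. State that no conclusion of balanced attrition will be drawn from a non-significant test.

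The sponsor gives up a favourable statement it cannot support, replaces one planned test and does minor extra tabulation. No visit, sample size or session changes.

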*Adaptation to chronic disease:* The Chronic Respiratory Disease Questionnaire (CRQ-SAS) [68] assesses aspects related to the adaptation to the disease (scale validated for the Spanish adolescent population by Valero et al. [69]). The psychometric properties are adequate (α = 0.85). The questionnaire on the adaptation to type 1 diabetes (RAE) [70] assesses aspects related to the adaptation to the disease, such as severity, adherence, psychological impact, discomfort, and health behaviours. Psychometric properties are adequate (α = 0.77). Finally, the Adolescent Rhinoconjunctivitis Quality of Life Questionnaire (AdolRQLQ) [71] is a quality of life assessment instrument specifically designed for the paediatric population with rhinoconjunctivitis. This questionnaire shows adequate psychometric properties (α = 0.77);*Parenting style of parents*: The Scale for the Evaluation of the Educational Style of Parents of Adolescents (EP) [72] allows for the assessment of the perception that adolescents have of their parents’ educational style;*Psychological well-being*: The Psychological Well-Being Scale for Adolescents (BIEPS-J) is a self-report measure developed [73] to determine the level of psychological well-being in adolescents (scale validated for the Spanish population [74]).

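### The named MANCOVA discards any participant missing one entered pre or post score; a mixed model per outcome would keep partial records

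*Protocol article*

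**What the plan says.** Under Statistical Methods (section 2.8) the protocol article names its analysis of change: "multivariate and univariate covariance analyses (MANCOVA and ANCOVA) were performed to identify changes in the post-intervention scores", "while controlling for the pre-intervention scores (covariate"). Each outcome therefore needs a pre and a post value. On software it says "These analyses were performed with the statistical package SPSS V.26". The same section adds hierarchical regressions that use one outcome's pre-intervention score and its change.

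On missing values, the stated step is t-tests and chi-square tests "to determine pre-intervention differences between participants with and without missing values in the variables studied". The section also compares dropout numbers between groups.

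Section 2.4 lists four primary patient instruments that apply to every adolescent: HADS, ESCQ-21, BIP-Q and RSE. Adaptation to the disease is a secondary outcome measured by three instruments: "The Chronic Respiratory Disease Questionnaire (CRQ-SAS) [68] assesses aspects related to the adaptation to the disease"; "The questionnaire on the adaptation to type 1 diabetes (RAE) [70] assesses aspects related to the adaptation to the disease"; and "the Adolescent Rhinoconjunctivitis Quality of Life Questionnaire (AdolRQLQ"). Section 2.4 also says that only the primary variables will be analysed if there are too few participants.

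Sections 2.1 and 2.5 make each participant their own control. T1 to T2 is the untreated period and T2 to T3 the treated period, each of about six months. (Section 2.4 numbers the same three visits from T0; the labels of section 2.1 are used here.) Section 2.6 puts the main study at about 200 adolescents.

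**The concern.** MANCOVA analyses a vector of outcomes at once. In its standard form a participant with one empty cell among the entered outcomes or covariates leaves the analysis entirely, including the scores that were observed. Testing whether those with and without gaps differ beforehand may show that the remaining sample is selected, but the analysed set stays the same.

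Two things are at stake. Precision falls in a study whose Discussion already expects that numbers may be small. And if families who are struggling leave more gaps, the remaining participants are those doing better, so the estimated benefit could be biased.

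The adaptation outcome raises a related question. Its three questionnaires are written for different diseases, so their scores are not interchangeable, and few adolescents would be expected to have all three.

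**Working it through.** The article gives no missingness rate, no complete-case count and no derivation of the 200, so there is no figure to reproduce. What follows is an illustration with assumed rates.

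**Inputs**
- N = 200 (section 2.6).
- Four primary patient instruments (section 2.4), each needed before and after treatment (Statistical Methods): k = 4 × 2 = 8 instrument-visits.
- One outcome in a univariate ANCOVA: k = 2.
- Missingness p per score: assumed 2% to 5%, independent across scores.

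**Formula.** Share retained = (1 - p)^k; share lost = 1 - (1 - p)^k.

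| Analysis | k | p = 2% | p = 5% |
|---|---|---|---|
| ANCOVA, one outcome | 2 | 0.98^2 = 0.960; 192 kept, 4% lost | 0.95^2 = 0.903; about 181 kept, 10% lost |
| MANCOVA, four primary instruments | 8 | 0.98^8 = 0.851; 170 kept, 15% lost | 0.95^8 = 0.663; 133 kept, 34% lost |

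If subscales are entered instead (HADS 2, ESCQ-21 3, BIP-Q 1, RSE 1, so k = 7 × 2 = 14), the same formula gives 151 and about 98 kept, a loss of 25% and 51%. Subscales of one form tend to be missing together, so this is an upper illustration.

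**Gaps by whole visit.** If a missed visit empties every instrument at once, the loss equals the share missing a required visit. With 10%, 20% or 30% missing one, 180, 160 or 140 of 200 remain, and the number is the same for MANCOVA and for ANCOVA. The excess loss from MANCOVA then disappears. A mixed model would still use the visits these participants did attend.

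**Adaptation questionnaires.** Under an assumed equal split of the sample over the three diseases, analysis within disease group has 200/3, or about 67, adolescents per questionnaire before other gaps. A joint model of all three could use only those who complete all three: 0 of 200 with no overlap, 10 at an assumed 5% and 20 at an assumed 10%. The article does not state such a joint model. The comparison shows only why the within-disease analysis should be written down.

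**The case against.** The strongest reply has four parts.

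1. *Missing-data methods and the list of variables in a multivariate test are details that an article may leave to the full protocol or SAP.* This stands as far as it goes: the absence of an imputation method is no finding. But the article does name the method, and deletion of incomplete records follows from that method.

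2. *A reader might infer that the whole plan uses only participants complete on every score.* The article does not say so. Complete-case restriction is a consequence of standard MANCOVA. The univariate ANCOVAs and the hierarchical regressions need only one outcome's own scores, so participants lost from the MANCOVA remain in those analyses. It is from the regressions that the article says it will attribute change to the programme. This part stands and confines the point to the MANCOVA.

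3. *A reader might infer that the adaptation analysis will have almost no complete cases.* Nothing in the article puts the three questionnaires into one model. The natural reading is one questionnaire per disease; the outcome is secondary and may be dropped; and the primary instruments are common to all patients. The primary outcomes are not affected.

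4. *The mixed model changes the question.* It does replace an adjusted post score by a difference between two changes. That difference is the comparison of untreated and treated periods for which sections 2.1 and 2.5 set up the three visits, so the change suits the design. It does not remove bias if gaps depend on unobserved distress, and it leaves the separate exclusion for low session attendance (section 2.3) as it is.

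**Conclusion.** The point holds for the MANCOVA step: it discards partial records, and the planned comparison of participants with and without missing values does not repair that. The size depends on rates that the documents do not give. At an assumed independent 2-5% per score, the four-instrument MANCOVA loses about 15-34% of 200, while a single-outcome ANCOVA loses 4-10%.

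A reader who counts eight primary scores before and after (16 values) could reach 28-56% (1 - 0.98^16 and 1 - 0.95^16). The documents do not support that as a headline. Eight is reached only by counting the HADS global score beside the two subscales it is formed from, and section 2.7 has the recruitment battery completed in a single session, which makes gaps by whole visit plausible. Under that pattern the number of scores no longer matters.

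The remedy is cheap and fits the design, so the change is worth making. The adaptation questionnaires need only a statement that each is analysed in its own disease group.

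**What to change.** Replace the MANCOVA/ANCOVA step by one linear mixed model per outcome:
- enter all available T1, T2 and T3 values, with visit as a fixed effect and a participant random effect;
- estimate (T3 - T2) - (T2 - T1), the change over the treated period minus the change over the untreated period;
- drop nobody for a gap on another instrument or at another visit.

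Analyse CRQ-SAS, RAE and AdolRQLQ each only within its own disease group. The comparison of participants with and without missing values can stay as a description.

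The cost is a rewording of the analysis section. No extra data or visits are needed, since all three assessments are already planned. There is no longer a single multivariate test statistic, and validity still rests on data being missing at random given the observed scores.

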### 2.1. Study Setting

This study will be conducted in the different leading hospitals of the Valencian Community, in the Pneumology, Endocrinology, and Allergology units. This study is a quasi-experimental design with repeated measures. Each participant receiving the intervention (experimental condition)will also act as their control grorup. Therefore, the physical and psychological diagnostic measures will be collected from all of participants in an initial assessment (T1) and, secondly, six months after the initial assessment and right before starting the treatment programme (T2). At these two assessment points (T1 and T2), all participants (patients and family members) will be assessed (T2). The treatment lasted for five sessions for adolescents, with one individual session per month and two sessions for family caregivers (month 4 and month 5). The treatment programme will begin in the maximum expected time of 15 days from the second pre-treatment assessment (T2), with an estimated duration of 5 months. After the end of the treatment sessions for the patient and their family members, a new diagnostic test (T3) will be conducted (across all variables), within an expected maximum time of 15 days until the end of the treatment, to assess the post-treatment change. Thus, the estimated time between T1 and T2 is the same as that between T2 and T3, which is six months. The programme of registration, interventions, and evaluations (SPIRIT Programme) is shown in Table 1 and Table S1. 

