### 2.2. Patient and Public Involvement

Participants will be recruited when receiving hospital care. Inclusion criteria will be (1) participants must be adolescents from 12 to 16 years of age, with (2) a diagnosis of CD (endocrinologic, such as DM1, or pneumo allergic diseases) within the last 6 months. Exclusion criteria will be (1) the presentation of a psychiatric disorder prior to the disease; (2) epilepsy, infantile cerebral palsy, or brain tumours; and (3) not understanding the Spanish language. All the parents of recruited adolescents will be offered the opportunity to participate in shorter sessions to promote self-care and family bonding. The parent training will be conducted in two 2-h sessions. The trainers will be psychologists specialised in health psychology who, prior to the start of the program, will receive hours of training in the 10Vida program.

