Despite the strengths and potentials of the study, especially its multicentre scope and its ability to adapt to different pathologies suffered by adolescents, which will allow for the comparison of results between groups, this study has certain limitations. The fact that the control group is a waiting list control group may mean that the results are not directly attributable to the intervention programme. In addition, the samples we intend to access are difficult to access, and the study will not compensate participants financially, so the number of participants may be small. Nevertheless, the team will try to encourage the motivation of adolescents and their families to participate, and will widely disseminate the programme to try to reach as many participants as possible.

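### The section 2.8 regression ignores trainers, whose differences arise only in the treated window, so its standard error is too small if each trainer treats several families

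*Protocol article*

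**What the plan says.** All families wait six months and are then treated. Section 2.5 puts the programme into effect "in the same sample as in phase II", so every participant supplies an untreated window (T1 to T2) and a treated window (T2 to T3).

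Section 2.2 describes who delivers it: "The trainers will be psychologists specialised in health psychology", trained in 10Vida beforehand. It does not say how many there are, how many families each will see, or how families are assigned. Section 2.3 gives five individual sessions per adolescent and two for caregivers. Section 2.6 plans a main study of about 200 adolescents and their families.

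The Statistical Methods part of section 2.8 states the model. "Firstly, the pre-intervention assessment score (control variable) was introduced, and then the experimental condition", coded "1 = experimental intervention group, 0 = control group) was introduced as an independent variable". "The dependent variable was the change variable between pre- and post-interventions", with a second change, to follow-up, also named. If the condition term is significant after adjustment for the pre-score, the article credits the change to the intervention. The registry items listed in section 2.8 include no trainer code.

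**The concern.** The model has two terms and treats every change score as independent of every other. At seven sessions per family, 200 families need 200 × 7 = 1,400 sessions. Unless there are nearly as many psychologists as families, each will carry a caseload, and families with the same trainer will tend to share part of their response.

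The own-control design removes whatever is common to both windows. A trainer has no counterpart in the waiting window, because nobody is being trained then. Trainer variation therefore enters the T3 score alone and stays whole in the contrast between the two changes. It averages out over the number of trainers, not over the number of families, whereas the stated standard error assumes the latter.

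The article's inference rests on the significance of that one term. A few trainers who happen to do better than average could make it significant although the programme has no average effect.

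**Working it through.** **No planned figure to reproduce.** The article gives no significance level, power, standard deviation, intraclass correlation or sample-size formula. The check below shows how the error rate depends on the missing quantities.

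**Inputs**
- From the article: N about 200 (section 2.6); model terms and coding (section 2.8); both windows from the same people (sections 2.1 and 2.5).
- Assumed: two-sided 5% test; outcome variance 1 at each visit; equal correlation ρ = 0.5 between visits; trainer variance τ² of 0.02 or 0.05 at T3 only; K = 20, 8 or 4 trainers with equal caseloads m = 200/K; no programme effect and no trend.

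**Step 1: pair each person's windows.** The contrast is D = (T3 − T2) − (T2 − T1) = T3 − 2·T2 + T1. Its weights sum to zero, so the person-level variance is (1 + 4 + 1)(1 − ρ) = 6 × 0.5 = 3.

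**Step 2: correlation of D within trainer.** ICC(D) = τ²/(3 + τ²), which is 0.02/3.02 = 0.0066 or 0.05/3.05 = 0.0164.

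**Step 3: variance ratio and error rate.** Ratio = 1 + (m − 1) × ICC(D). False-positive rate = 2{1 − Φ(1.96/√ratio)}. For example, with 8 trainers and τ² = 0.05: 1 + 24 × 0.0164 = 1.39; 1.96/√1.39 = 1.66; rate 9.7%.

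The last two columns are rejection rates from a simulation of 6,000 trials per row. The stated regression uses both windows as separate rows (change on pre-score and 0/1 condition).

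| Trainers | m | τ² | Ratio | Paired, formula | Paired, simulated | Stated regression, simulated |
|---|---|---|---|---|---|---|
| 20 | 10 | 0.02 | 1.06 | 5.7% | 6.3% | 9.2% |
| 20 | 10 | 0.05 | 1.15 | 6.7% | 7.0% | 10.6% |
| 8 | 25 | 0.02 | 1.16 | 6.9% | 6.9% | 10.9% |
| 8 | 25 | 0.05 | 1.39 | 9.7% | 9.4% | 15.9% |
| 4 | 50 | 0.02 | 1.32 | 8.9% | 9.0% | 14.5% |
| 4 | 50 | 0.05 | 1.80 | 14.4% | 14.2% | 23.9% |

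**Step 4: separate the two causes.** With no trainer effect, the paired test rejects in 5.0% and the stated regression in 6.9%. That excess comes from treating one person's two windows as independent and is a different defect. The paired columns are free of it and show the part due to trainers.

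**Step 5: what cancels.** With 8 clusters that differ only by a constant level (5% of variance at every visit), the paired test rejects in 5.1%, which is nominal. The stated regression rejects in 7.1%, about the same as with no clusters.

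**Step 6: does respecting trainers restore the level?** A t-test on the K trainer means of D, with K − 1 degrees of freedom, rejects in 4.6–5.4% across all the rows.

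**Sensitivity.** With ρ = 0.7 the person-level variance of D falls to 6 × 0.3 = 1.8, and the formula gives 6–8% with 20 trainers, 8–13% with 8 and 11–20% with 4. If the visit correlation decays with time instead of being equal, the stated regression is close to nominal (4–6%) without trainer effects. With 5% of residual change variance due to trainers and N = 200, it then rises to about 23–24% with 3 trainers, 11% with 10 and 7–8% with 20.

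**The case against.** The strongest reply is that the decisive facts are absent. The article does not say that trainers are few or that any of them has a large caseload. With 20 or more trainers, or very small trainer differences, the rate is close to 5%. That stands, and it is why the size can only be given as a range.

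A second reply is that a condensed article commonly leaves a therapist or centre term to the full plan. That would carry weight if section 2.8 were silent. It instead writes out a specific two-term model and a rule for attributing the result, and followed as written these give the wrong standard error wherever trainers share families.

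Third, trainers could be treated as fixed, so that the result concerns only those who took part. That is coherent, but the article presents the programme as a tool for routine practice, which implies other trainers.

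A reader might also infer three stronger things that the article does not support:
- **Hospital or unit differences pass as programme effect.** Every unit supplies both windows, so stable differences cancel. Only a disturbance specific to a unit and a visit would remain, and nothing in the article gives its size.
- **Each trainer sees one unit's patients.** The figure of "25–30 patients from each unit" is a pilot size, not a caseload. Delivery is individual and has moved online, and nothing ties a trainer to a unit.
- **A planned test between diseases is invalid.** The Discussion says of the design: "its ability to adapt to different pathologies suffered by adolescents, which will allow for the comparison of results between groups". Section 2.8 specifies no such test, so there is no stated analysis with an error rate to compute.

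**Conclusion.** The point holds in a limited form. Trainer differences act only in the treated window, survive the own-control contrast and are ignored by the stated model. The effect estimate is not biased; its precision is overstated. Under the assumptions above (N about 200, ρ = 0.5, trainer variance 2–5%), correct pairing alone leaves a false-positive rate of about 5–7% with 20 trainers, 7–10% with 8 and up to about 15% with 4. For the regression as written, the corresponding rates are about 9–11%, 11–16% and 15–24%, and part of that excess belongs to the missing pairing. How serious this is depends on a trainer count that the sponsor knows and the article does not give. The change is worth making because it is cheap, and because the trainer's identity may be hard to recover if it is not recorded as sessions are given.

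**What to change.** In section 2.8, replace the two-step regression for each primary outcome with one of these:
- a repeated-measures model for the T1, T2 and T3 scores with a participant effect and a random trainer effect acting on the treated window only. Trainers should not be nested in units unless they are in fact tied to units; or
- the paired contrast of the two changes, with standard errors clustered by trainer and a small-sample correction based on the number of trainers.

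A trainer term added to the present regression would not be enough, because the two windows of one person would still be treated as independent.

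Add a trainer code for each family to the existing registry, and state the expected number of trainers. Call any comparison between pathologies descriptive.

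The cost is wording and one code per family, with no extra patients or visits. Intervals become wider. With K − 1 degrees of freedom, the 5% critical value rises from 1.97 (199 degrees of freedom) to 2.09 with 20 trainers, 2.36 with 8 and 3.18 with 4, in addition to the larger standard error. With only a few trainers this is a marked loss of precision, and the sponsor should know it before the main study.
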